### 4.3.2 Data collection and investigators

The data collection will be carried out by trained and blinded raters (doctors, physiotherapists) at baseline, post-intervention and at the follow-up call. After the end of the intervention, the participants' experience and acceptance of the intervention will be assessed in focus groups. A follow-up call will take place one month after the end of the intervention, i.e. two months after the baseline assessment. This survey will include a very short interview, the fall rate during the 4-week intervention period and two questionnaires (FOGQ, FES-I).

### 4.3.3 Primary and secondary endpoints and survey instruments

Table 2 lists the primary and secondary endpoints of the study with the respective survey instruments selected. All assessments are used in their validated German version. The implementation and psychometric criteria of the clinical assessments are described in chapter 4.4.

**Table 2:** Primary and secondary endpoints and survey instruments

| Endpoint                                                                                  | Survey                                                                                                       | Scr | BL | Int. | PI | FU
Call |
|-------------------------------------------------------------------------------------------|--------------------------------------------------------------------------------------------------------------|-----|----|------|----|------------|
| Primary clinical endpoints                                                         |                                                                                                              |     |    |      |    |            |
| Dynamic balance                                                                           | Functional Gait Assessment (FGA)                                                                             |     | X  |      | X  |            |
| Dynamic balance with eye movements (saccade speed, amplitude, latency, fixation duration) | Items 5, 6 and 10 of the Functional Gait Assessment (FGA) with mobile eye tracking using Tobii Pro Glasses 3 |     | X  |      | X  |            |
| Secondary clinical endpoints                                                       |                                                                                                              |     |    |      |    |            |
| Cognitive function                                                                        | Mini-Mental State Test (MMST)                                                                                | X   |    |      |    |            |
| Functional mobility                                                                       | Timed-Up-and-Go (TUG)                                                                                        |     | X  |      | X  |            |
| Functional mobility with manual dual task                                                 | Timed-Up-and-Go with manual dual task (TUGman)                                                               |     | X  |      | X  |            |
| Static and dynamic equilibrium                                                            | Berg Balance Scale (BBS)                                                                                     |     | X  |      | X  |            |
| Dynamic balance                                                                           | Four Square Step Test (FSST)                                                                                 |     | X  |      | X  |            |

|                                                                                                                                          |                                                                                                                           |  |   |   |   |   |
|------------------------------------------------------------------------------------------------------------------------------------------|---------------------------------------------------------------------------------------------------------------------------|--|---|---|---|---|
| Walking speed                                                                                                                            | 10-Metre Walk Test (10MWT)                                                                                                |  | X |   | X |   |
| Health-related quality of life                                                                                                           | Parkinson's Disease Questionnaire-39 (PDQ-39)                                                                             |  | X |   | X |   |
| Freezing of Gait                                                                                                                         | Freezing of Gait Questionnaire (FOGQ)                                                                                     |  | X |   | X | X |
| Fall-associated self-efficacy                                                                                                            | Falls Efficacy Scale (FES-I)                                                                                              |  | X |   | X | X |
| Depression                                                                                                                               | Beck Depression Inventory-II (BDI-II)                                                                                     |  | X |   | X |   |
| Fall rate                                                                                                                                | Number of falls (a) in the 3-month period before study entry (BL), (b) intervention period (PI) and (c) 4-week follow-up. |  | X |   | X | X |
| Feasibility of a larger randomised controlled trial                                                                                      |                                                                                                                           |  |   |   |   |   |
|                                                                                                                                          | Recruitment rate                                                                                                          |  | X |   |   |   |
|                                                                                                                                          | Retention rate                                                                                                            |  |   |   | X | X |
|                                                                                                                                          | Adherence rate                                                                                                            |  |   | X |   |   |
|                                                                                                                                          | Adverse events                                                                                                            |  |   | X | X |   |
|                                                                                                                                          | Acceptance of the intervention (continuous: narrative; focus groups in intervention group 1)                              |  |   | X | X |   |
| Eye movements during the intervention in group 1: standardised exercises, each at the end of week 1-4, during exercise 2, 3, 4, 6 and 7. | Measured for 12 min: saccade velocity, amplitude, latency, fixation time (Tobii Pro Glasses 3)                            |  |   | X |   |   |
| Abbreviations: Scr=Screening; BL=Baseline; Int.=Intervention period; PI=Post-intervention-; FU=Follow-up- testing.                       |                                                                                                                           |  |   |   |   |   |

#### 4.3.3.1 Mobile eye-tracking glasses (Tobii Pro Glasses 3)

##### 4.3.3.1.1 Use and application of the mobile eye-tracking glasses

The use and application of the Tobii Pro Glasses 3 eye-tracking glasses is as follows:

Eye-tracking glasses from Tobii AB are used to record the eye movements. The Tobii Pro Glasses 3 carry the CE marking and comply with the applicable health and safety regulations of the European Union. The Tobii Pro Glasses 3 and their handling comply with the following standards:

- EMC Emission: EN55022:2010 Class B, FCC part 15, Class B
- EMC Immunity: EN55024:2010
- SAR EN62311:2008
- Low Voltage Directive 2006/95/EEG
- EMC Directive 2004/108/EC
- Radio and Telecommunications Terminal Equipment Directive (R&TTE) 1999/5/EC
- RoHS Directive 2002/95/EC
- RoHS2 Directive 2006/121/EC
- WEEE Directive 2002/121/EC
- Reach Directive 2006/121/EC
- IEC/EN/UL60950-1:2005 (Electrical safety for global/EU/US)

(ETL Compliance: Conforms to ANSI/UL Std. 60950-1 Certified to CSA Std. C22.2 No. 60950-1; Canadian Compliance Statement: CAN ICES-3(B)/NMB-3(B))

The Tobii Pro Glasses 3 will be worn by the participants for the assessment (items 5, 6 & 10 of the FGA) at all assessment times and during the intervention at the last therapy session from week 1-4 for about 12 minutes each. Before the start of the tests, the participants are informed by the responsible examiners or therapists about the use of the eye-tracking glasses and about possible side effects such as temporary dizziness. The participants will be secured by the physiotherapists at all times. Should this be the case at any time, the examiner or therapist in charge will immediately switch off the glasses and the participants will remove them.

#### **4.3.3.1.2 Technical data of the Tobii Pro Glasses 3**

The Tobii Pro Glasses 3 have 16 illuminators and four eye cameras (two for each eye) integrated into the scratch-resistant lenses for optimal positioning and an unrestricted field of vision. The sampling rate is 50 or 100 Hz. The one-point method is used for calibration. The scene camera, video resolution is 1920 × 1080 at 25 fps. The total weight of the glasses (incl. cable) is 76.5 grams. The scene camera has a wide field of view (106° horizontal: 95°, vertical: 63°). With the help of the built-in accelerometer, gyroscope and magnetometer sensors, it is possible to obtain separate information on head and eye movements and to better filter the influence of head movements on the eye-tracking data. In addition, the Tobii Pro Glasses 3 have a wide range of nose pads, as well as corrective lenses for people with low vision, to ensure an optimal fit and wearing comfort.

#### **4.3.3.1.3 Safety precautions for the eye-tracking examination**

The eye-tracking glasses emit pulsed infrared (IR) light via the 16 illuminators to support the eye-tracking sensors. Certain medical and other devices are susceptible to interference from IR light. Therefore, before using the Tobii Pro Glasses 3, it is important to ensure that subjects do not need to use such sensitive devices, as their accuracy or proper functioning may be affected.

The examination with the Tobii Pro Glasses 3 lasts 12 min during the intervention 1x/week and about 5 min during the baseline and post-intervention assessments.

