| DRKS ID                | As soon as the Ethics Committee has given its approval, registration in the DRKS or another primary registry is applied for in accordance with the WHO criteria.                                                                                                                                                                                                                                                                                                                                                                                                                                                                                                                                  |
| Study objective        | The study objective is to investigate the effects of an activity-based physiotherapy training programme with eye movement training compared to an activity-based physiotherapy training programme without eye movement training on dynamic balance, mobility with and without multi-task, static and dynamic balance walking speed, health-related quality of life, freezing of gait, fall-associated self-efficacy, depression and fall rate. The aim is also to explore the change in eye movements (saccade velocity, amplitude, latency, fixation duration) over the intervention period and to evaluate the feasibility of a larger randomised controlled trial using predefined parameters. |
| Primary endpoints      | 1.1 Dynamic balance measured by the Functional Gait Assessment (FGA)

1.2 Items 5, 6 and 10 of the FGA are additionally performed with eye-tracking glasses (Tobii Pro Glasses 3) for mobile measurement of eye movements (saccade velocity, amplitude, latency, fixation duration).                                                                                                                                                                                                                                                                                                                                                                                                        |

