### 2.3 Study objectives

Thus, four **study objectives** are pursued to deepen the knowledge on effectiveness:

1. Assessment of the effects on dynamic balance (primary endpoint)
2. Investigating the feasibility of a larger randomised controlled trial
3. assessment of the effects on functional mobility with and without manual multi-task, static and dynamic balance, walking speed, health-related quality of life, freezing of gait, fall-associated self-efficacy, depression and fall rate (secondary endpoints).

4. evaluation of the change in eye movements during the intervention, measured once a week in the intervention group over the intervention period.

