## 2.4 Null hypotheses

**Primary null hypothesis:** There is no difference between the effects of an everyday physiotherapy training programme with eye movement training and such a training programme without eye movement training on dynamic balance in people with idiopathic Parkinson's syndrome.

**Secondary null hypotheses:** There is no difference between the effects of an everyday physiotherapy training programme with gaze movement training and such a training programme without gaze movement training on functional mobility with and without manual multi-task, static balance, walking speed, health-related quality of life, freezing of gait, fall-associated self-efficacy, depression, fall rate and eye movements during dynamic balance tasks and specific training items in individuals with Idiopathic Parkinson's Syndrome.

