#### **4.4.15 Measurement of eye movements during the intervention**

Once a week, at the last therapy session, the eye movements are measured for 12 minutes using Tobii Pro Glasses 3: saccade speed, amplitude, latency and fixation time. This measurement is done after a 5-minute warm-up (warm-up: see Instructor Manual, Appendix 1).

The 12-minute period was chosen because it is expected that the participants will have a familiarisation phase with the Tobii glasses of about 5-6 minutes (communication with Tobii). The data obtained are thus more reliable and closer to reality. Data collection will be done during the performance of standardised exercises to allow for comparison: Exercise 2, 3, 4, 6 and 7.

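### The FGA eye-tracking recording (endpoint 1.2) lasts about 5 minutes with no wear-in described, although the protocol expects 5-6 minutes of familiarisation with the glasses; weekly wear in group 1 only may add a difference between the arms

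*Protocol*

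**What the plan says.** The synopsis lists two primary endpoints: 1.1, the FGA, and 1.2, for which "Items 5, 6 and 10 of the FGA are additionally performed with eye-tracking glasses" to measure saccade velocity, amplitude, latency and fixation duration. Table 2 (section 4.3.3) schedules 1.2 at baseline and post-intervention. Section 4.3.3.1.3 gives the duration: the examination "lasts 12 min during the intervention 1x/week and about 5 min during the baseline and post-intervention assessments".

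Section 4.4.15, which covers the weekly recordings during training, explains why 12 minutes were chosen: "it is expected that the participants will have a familiarisation phase with the Tobii glasses of about 5-6 minutes". It continues: "The data obtained are thus more reliable and closer to reality".

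On who is recorded in training, Table 2 has the row "Eye movements during the intervention in group 1", and objective 4 in section 2.3 says "measured once a week in the intervention group over the intervention period". Section 4.3.3.1.1 says the glasses are worn "during the intervention at the last therapy session from week 1-4 for about 12 minutes each", but speaks of participants without naming an arm. The secondary hypotheses in sections 2.4 and 2.5 compare the two arms on "eye movements during dynamic balance tasks and specific training items".

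Section 5.6.1 analyses the eye-movement variables, as metric data, with a 2 x 2 ANOVA of time (baseline, post-intervention) by group.

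**The concern.** The protocol recognises a measurement problem, that people need some minutes to get used to the glasses, and guards against it in the weekly training recording, a secondary measure. It does not carry the same allowance over to the FGA recording, which is listed as primary and is the one compared between the arms. What is recorded there may be behaviour during familiarisation, which by the protocol's own reasoning is less reliable.

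A second issue follows from the schedule. If only group 1 wears the glasses during training, the arms reach the post-test with very different experience of the device. A difference in change between the arms could then contain some device familiarity as well as any effect of gaze training. Section 5.6.1 uses the between-group results to look for trends in effectiveness and as a basis for the sample size of a larger trial, so such an artefact could carry forward.

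**Working it through.** The protocol gives durations but no derived figure on this point, so there is nothing to reproduce first. The check is arithmetic on those durations.

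**Inputs**
- FGA eye-tracking examination: about 5 min at each of two visits (section 4.3.3.1.3).
- Expected familiarisation: about 5-6 min (section 4.4.15).
- Training recording: 12 min, last session of each of weeks 1-4 (sections 4.3.3.1.1 and 4.4.15), in group 1 (section 2.3 and Table 2).
- Post-test: 4 weeks after the start of the intervention (section 4.2.1, Table 1), taken here to follow all four weekly recordings.
- Wear-in before items 5, 6 and 10: none described in sections 4.3.3.1.1, 4.3.3.1.3 or 4.4.2.

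**Step 1: recording time left after familiarisation** = max(0, recording time - familiarisation time)

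| Recording | Familiarisation 5 min | Familiarisation 6 min |
|---|---|---|
| FGA, 5 min | 5 - 5 = 0 min | 5 - 6 < 0, so 0 min |
| Training, 12 min | 12 - 5 = 7 min | 12 - 6 = 6 min |

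At baseline nobody has worn the glasses in the study before, so 0 minutes remain in both arms.

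**Step 2: wear before the post-test**
- Group 1: 4 x 12 = 48 min in training, plus about 5 min at baseline = about 53 min.
- Group 2: 0 min in training, plus about 5 min at baseline = about 5 min.
- Ratio: 53 / 5 = 10.6.

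**Step 3: what this means at the post-test.** The answer depends on whether familiarisation carries over between sessions, which the protocol does not say.

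| Assumption | Group 1 at post-test | Group 2 at post-test | Consequence |
|---|---|---|---|
| Starts again each session | 0 min usable | 0 min usable | Poorer data in both arms, no difference between arms from this source |
| Accumulates without loss | phase complete (53 min exceeds 5-6 min) | 5 - 5 = 0 or 6 - 5 = 1 min of the phase left | Small difference between arms; baseline still affected |
| Partly fades | last wear in week 4 | last wear about 4 weeks earlier | Arms differ by an unknown amount |

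The baseline recording falls inside the phase in all three rows. A material difference between the arms arises only in the third.

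**The case against.** The strongest objection concerns the difference between the arms. Section 4.4.15 sets 12 minutes for every weekly recording, week 4 as much as week 1, which fits a phase expected afresh each time. Both arms would then be recorded under the same handicap at both visits. With full carry-over, group 2 has used nearly all of the phase at baseline. Only partial fading gives a real difference, and the protocol does not document it. This stands, and it limits the second issue to a possibility. It does not touch the first: the baseline recording falls inside the phase under every assumption.

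The protocol is also not uniform on who wears the glasses in training. Section 4.3.3.1.1 names no arm, and the hypotheses in sections 2.4 and 2.5 need group 2 recordings if the arms are to be compared on training items. If group 2 were recorded weekly as well, the imbalance would disappear. The explicit statements in section 2.3 and Table 2 favour group 1 only, but the conflict is real.

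The weight of 1.2 is open to argument too. The synopsis and Table 2 call it primary, whereas section 2.3 names dynamic balance as the primary endpoint, sections 2.4 and 2.5 place eye movements among the secondary hypotheses, and section 5.6.1 calls the inference preliminary.

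Some stronger readings are tempting but unsupported:
- A reader might infer that the bias favours group 1. No section says which way familiarity moves saccade velocity, amplitude, latency or fixation duration.
- A reader might infer an inflated false-positive rate of some given size. The protocol gives no size for the familiarisation effect, so no rate can be derived.
- A reader might think that ease with the glasses reveals the arm to the rater. Nothing in the protocol indicates this, and group 2 has worn them at baseline.
- A reader might conclude that analysis can do nothing. Comparing early with late minutes of group 1's 12-minute recordings would indicate how large within-session familiarisation is, although it would not remove the confounding with arm.

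**Conclusion.** The concern holds in two parts of different strength.

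First, the protocol's familiarisation allowance is not applied to endpoint 1.2. Taking its own durations at face value, and given that no wear-in is described, none of the roughly 5 minutes recorded at baseline lies beyond the 5-6 minute phase in either arm. The same may be true at the post-test.

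Second, if weekly wear is confined to group 1, as section 2.3 and Table 2 state, prior wear at the post-test is about 53 versus about 5 minutes, and the group-by-time contrast for 1.2 may partly reflect unequal familiarity. Size and direction are undetermined, because carry-over between sessions is not addressed.

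The point is confined to 1.2. Items 5, 6 and 10 are performed additionally with the glasses and used separately (section 4.4.2), so the FGA total under 1.1 is not affected. The change is worth making before the first patient, because recordings already taken without wear-in cannot be repaired.

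**What to change.** 1. In both arms and at both visits, fit and calibrate the glasses at least 6 minutes before FGA items 5, 6 and 10, and analyse only data recorded after that. A seated questionnaire can fill the time; the PDQ-39 takes 10-20 minutes (section 4.4.9.1).
2. Reconcile section 2.3 and Table 2 (group 1 only) with sections 2.4 and 2.5 (arms compared on training items) and section 4.3.3.1.1 (participants, no arm named).
3. If group 2 does not wear the glasses in training, state that the arm contrast for 1.2 may be confounded with familiarity with the device.

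The cost of item 1 is a few more minutes of wear at two visits, with the possible temporary dizziness that section 4.3.3.1.1 already mentions. Items 2 and 3 are changes of text.

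Giving group 2 the same weekly wear would equalise exposure, but it is optional. It adds four fittings per control patient, and the protocol does not say how many devices or how much therapist time are available.
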